#### UGT1A1 genotyping in blood samples and adaptation of irinotecan dose intensity

Before treatment initiation, the *UGT1A1* genotype of the patient will be assessed in blood using Polymerase Chain Reaction (PCR). Patients will be genotyped for *UGT1A1*28* (TA repeat; rs3064744; NC_000002.12:g.233760235TA[5_11]). DNA for genotyping will be isolated from 200µl of whole EDTA blood obtained prior to start of therapy. Genotyping will be conducted using validated real-time PCR reactions with appropriate wild type, heterozygous and homozygous controls in every run. Genotypes will be converted to phenotypes in the following manner: homozygous carriers of *UGT1A1*28* are defined as UGT1A1 PMs, heterozygous carriers are considered UGT1A1 intermediate metabolizers (IMs) and *UGT1A1* wild type individuals are considered UGT1A1 normal metabolizers (NMs). In UGT1A1 PMs the irinotecan starting dose will be reduced by 30% and further individualized in subsequent cycles of treatment based on ANC and clinical tolerance. The starting dose in UGT1A1 NMs and IMs will be left unchanged. Further dose modifications or treatment delays will be applied according to standard of care protocols and guidelines.

#### Quantification of bacterial GUS activity and gut microbiota composition in fecal samples

Fecal samples will be collected at home using a patient-friendly, and easy-to-use collection kit. At each time point, patients are asked to fill two fecal collection tubes with spoons attached to the lid (Sarstedt, Nümbrecht, Germany) and to immediately store samples in a freezer at home, until their next hospital visit. Cooled transporter container (Sarstedt, Nümbrecht, Germany) will be provided to the patients to ensure that the samples remain frozen during the transport to the hospital. Upon arrival in the hospital, samples will be temporarily stored at −20°C and at −80°C for long-term storage.

GUS activity in these samples will be quantified using an enzyme activity assay, which is based on the assay as described by Jariwala et al. and Bhatt et al. [15, 18] and which is currently under validation in our laboratories for the use with human fecal samples. In short, this assay consists of three steps: firstly, a pre-processing to remove unwanted debris, secondly a bicinchoninic acid (BCA) assay (Pierce™ BCA Protein Assay Kit, Thermo Fisher Scientific, USA) to determine the total protein concentration in the fecal lysate, and thirdly a fluorescence-based enzyme activity assay quantifying SN-38G-specific GUS activity. For the enzyme activity assay, fluorescent SN-38G is added to the fecal lysate and conversion to SN-38 during a period of one hour is quantified using a SpectraMax iD3 multi-mode microplate reader (Molecular Devices, San Jose, CA, USA). Subsequently, an online algorithm-based calculation tool (developed by the University of North Carolina, USA) will be used to calculate SN-38 reactivation rate as concentration over time (nM/min). Fecal levels of SN-38 and SN38-G will also be measured directly in fecal samples by means of a liquid chromatography-mass spectrometry (LC–MS/MS) assay.

Gut microbiota composition, diversity and functional capacity will be analyzed by means of whole metagenomic shotgun sequencing (WMGS). Fecal samples collected at baseline (T1) as well as during the first (T2) and fourth (T5) cycle of the irinotecan-based systemic treatment will be used for this analysis. From these samples, 150-250mg of feces will be weighted and metagenomic DNA will be isolated using the QIAamp DNA Mini kit (Qiagen, the Netherlands). In short, this procedure will consist of bead-beating with zirconia beads and the Fastprep™ instrument (MP Biomedicals, USA), followed by column-based DNA purification. Library preparation will be performed with the Illumina DNA Prep kit (M) (Illumina, USA). Subsequently, WMGS will be performed on a NovaSeq 6000 Illumina platform (sequencing depth > 10 Gb/sample, loading 300–600 pM). Filtered reads will be assembled into metagenome assembled genomes (MAGs) as well mapped to the HUManN3 database [20] to assed the functional capacity of the gut microbiomes of the samples. The MAG assembly, including a taxonomic and functional annotation of the MAGs will be done with the publicly available nf-core/mag pipeline [21, 22]. For the read-level annotation both a taxonomic as well as functional assigned using the HUMaN3 package [20] will be used to assess the general functionalities for the microbial communities. The datasets will be combined to obtain the functional potential and taxonomic composition of the gut microbiomes.

### Clinical data collection and management

#### Evaluation of tumor response

Tumor response will be evaluated based on standard care CT or MRI scans conducted at baseline (T1) and after the fourth cycle (T5) of irinotecan-based systemic therapy. Based on the percentage of change of target lesions, tumor response will be scored according to the Response Evaluation Criteria in Solid Tumors (RECIST, version 1.1 [23]) and will be classified as progressive disease, stable disease, partial response or complete response.

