#### Study population

Patients will be included via the oncologic outpatient clinics of the participating centers. Patients are eligible if they are ≥ 18 years of age, diagnosed with advanced CRC, and planned to start with irinotecan-based systemic treatment, if applicable in combination with anti-EGFR treatment. Additionally, patients must have a WHO performance status 0–2, minimal acceptable safety laboratory values at baseline, defined as: ANC of ≥ 1.5 × 109/L, platelet count of ≥ 100 × 109/L, serum bilirubin ≤ 1.5 × ULN, ALAT and ASAT ≤ 2.5 × ULN; in case of liver metastases ALAT and ASAT ≤ 5 × ULN, and renal function (eGFR) ≥ 50 ml/min or creatinine ≤ 1.5 × ULN.

Exclusion criteria are: microsatellite instability (MSI) or deficient MMR proteins, being pregnant or nursing, presence of an ileostomy, Asian ethnicity, other systemic treatment within < 1 month before inclusion, therapeutic antibiotic use within < 3 months before inclusion, abdominal radiotherapy within < 2 weeks before inclusion, being physically or mentally incapable or incompetent, more than 25% irinotecan dose reduction at the start of treatment (dose reductions during treatment are allowed), with exception of dose reduction in UGT1A1 PMs.

Patients can be treated with combination chemotherapy (FOLFOXIRI/FOLFIRI) or irinotecan monotherapy and will follow the regular treatment regimens, according to the Dutch guidelines (Table 1).

**Table 1 Tab1:** Overview of irinotecan-based treatment regimens

		**Compounds**	**Number of weeks per cycle**	**Possible addition of bevacizumab?**	**Possible addition of anti-EGFR?**
Treatment	FOLFOXIRI	Irinotecan 5-FU Folinic acid Oxaliplatin	2	yes	no
	FOLFIRI	Irinotecan 5-FU Folinic acid	2	yes	yes
	Monotherapy	Irinotecan	3	no	no

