### Statistical and bioinformatic analyses

#### Sample size calculation

The sample size calculation was based on having sufficient precision to estimate sensitivity and specificity of the GUS activity assay to predict late-onset GI toxicity. Literature shows that about 82% of patients treated with irinotecan experience diarrhea (all grades) [25], while approximately 18% develop grade 3–4 diarrhea [5, 6]. For estimation of sensitivity, we determined a maximum half-width of the 95% confidence interval (CI) of 17%, requiring a minimum of 22 patients with grade 3–4 diarrhea. To achieve this precision, a total of 84 patients need to be included, considering an estimated toxicity rate ranging from 16 to 22%. Out of these 84 patients, 62 individuals would not experience grade 3–4 diarrhea, allowing for the estimation of specificity with a 95% CI half-width of around 10%. Hence, the total number of patients required remains at 84. Considering an anticipated 20% drop-out rate, because of the advanced setting, 104 patients need to be included in the study.

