#### Statistical and bioinformatic analysis of main outcome parameters

The association between CMS subtypes 1–4 and treatment response (categorized as progressive disease, stable disease, partial response and complete response) will be analyzed using chi-squared tests. Survival analysis within the different CMS subtypes will be done by Kaplan Meier curves.

To validate the safety of the 70% irinotecan starting dose intensity, toxicity in UGT1A1 PMs will be compared to historical control patients, i.e. cohorts of patients described in literature that are homozygous polymorphic for *UGT1A1*28* and were treated with full dose therapy. In addition, toxicity in UGT1A1 PMs will be compared to UGT1A1 non-PMs treated with full dose in the current study, under the assumption that these groups experience comparable degrees of toxicity.

Correlations between GUS activity and the degree of experienced late-onset GI toxicity during irinotecan-based treatment will be analyzed by means of the Spearman correlation coefficient. Furthermore, we will investigate whether GUS activity is different between patients without diarrhea vs. grade 1–2 diarrhea vs. grade 3–4 diarrhea by means of ANOVA or the Kruskal Wallis test, depending on whether the data are normally distributed or not. Longitudinal changes in GUS activity during irinotecan-based treatment will be analyzed using repeated-measures ANOVA or the Friedman test.

Bioinformatic analysis of the predicted GUS functionality derived from metagenomics sequencing will be conducted. A Hidden Markov Model (HMM)-profile will be made per orthologous group with predicted GUS functionality, based on a reference dataset of publicly available GUS protein sequences and the results of Pollet et al. [12, 26]. The HMM-profiles will be used to identify all predicted proteins with a potential GUS functionality per fecal sample. These predicted proteins will be used to create a non-redundant microbial GUS protein catalogue.

Changes in GUS activity and overall gut microbiota composition, diversity and potential GUS capacity during irinotecan-based systemic treatment will be assessed by redundancy analysis (RDA) [27] and ANOVA [28]. These data will be used to examine the microbial GUS variation and origin per fecal community in order to link the microbial composition and GUS functional potential to the measured GUS activity.

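### Response has no value for patients who die or stop for progression before the T5 scan, so the CMS–response test can be biased in either direction

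*Protocol article*

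**What the plan says.** The section on evaluation of tumor response uses two routine scans, "conducted at baseline (T1) and after the fourth cycle (T5) of irinotecan-based systemic therapy". Scoring follows RECIST 1.1 and is "Based on the percentage of change of target lesions"; each patient "will be classified as progressive disease, stable disease, partial response or complete response". Table 2 agrees, with CT/MRI marked only at baseline and cycle 4.

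The section on analysis of the main outcome parameters carries the same four categories into the test of CMS 1–4: "treatment response (categorized as progressive disease, stable disease, partial response and complete response) will be analyzed using chi-squared tests". Survival by CMS subtype is shown separately with Kaplan-Meier curves.

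Table 1 ("Number of weeks per cycle") gives 2 weeks for FOLFOXIRI and FOLFIRI and 3 weeks for monotherapy. The section on sampling time points adds that delays may lengthen these intervals.

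The sample size section allows for an "anticipated 20% drop-out rate, because of the advanced setting", applied to the number needed for the sensitivity and specificity of the GUS assay.

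**The concern.** Predicting response from tumor markers is part of the first listed primary objective. The patients who say most about non-response are those whose disease kills them or ends treatment within the first cycles. The response variable needs a second scan to exist, and none of its four categories is assigned to a patient who has no such scan. If the definition is followed literally, these patients are not counted as failures. They leave the analysis.

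That loss is not random, because early failure is itself the worst outcome on the scale. Each subtype's response rate is then calculated among patients who stayed well enough to be scanned, and that share may differ between subtypes. A CMS comparison restricted in this way could show a difference that is too small, too large or not there at all.

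**Working it through.** **1. Time at risk before T5.** From Table 1: 4 cycles × 2 weeks = 8 weeks; 4 × 3 weeks = 12 weeks for monotherapy.

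**2. The plan's own figures.** No sample size, power or loss rate is given for the CMS–response test. The only related figure is the drop-out inflation: 84/(1 − 0.20) = 105, against 104 stated, so it reproduces closely. It belongs to the GUS calculation and is not used as an input below.

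**3. Formula.** Let p be the true response rate (partial plus complete) in a group, with early failures counted as progressive disease. Let e be the fraction of the group who fail before T5. No early failure is a responder, so the rate among scanned patients is p/(1 − e), and the observed difference is

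p₁/(1 − e₁) − p₂/(1 − e₂).

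- If e₁ = e₂ = e, this is (p₁ − p₂)/(1 − e), which is always wider than the truth.
- If p₁ = p₂ but e₁ ≠ e₂, it is not zero, so a false difference appears.
- It narrows only if early failure is sufficiently concentrated in the poorer-responding group.

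**4. Numbers.** Assumptions, none of them from the documents: N = 84, CMS4 share 25% against all other subtypes, two-sided 5% level, and a 2×4 chi-squared test (3 df) with power from the noncentral chi-squared distribution. The true category shares (PD/SD/PR/CR, %) are:
- A, C and F: CMS4 10/35/50/5, other 30/35/32/3.
- B: 15/30/50/5 and 30/35/32/3.
- D: 20/25/50/5 and 25/40/32/3.
- E: 25/35/37/3 in both groups.

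| | Lost before T5, CMS4 vs other | Response rates among scanned | True → observed difference (points) | Rejection rate, all patients → scanned only |
|---|---|---|---|---|
| A | 2% vs 15% | 0.55/0.98 = 56.1%; 0.35/0.85 = 41.2% | 20.0 → 14.9 | 36.7% → 17.1% |
| B | 10% vs 10% | 0.55/0.90 = 61.1%; 0.35/0.90 = 38.9% | 20.0 → 22.2 | 27.8% → 34.8% |
| C | 5% vs 15% (half of all PD) | 0.55/0.95 = 57.9%; 0.35/0.85 = 41.2% | 20.0 → 16.7 | 36.7% → 23.5% |
| D | 15% vs 5% | 0.55/0.85 = 64.7%; 0.35/0.95 = 36.8% | 20.0 → 27.9 | 25.1% → 42.7% |
| E | 2% vs 20%, no true difference | 0.40/0.98 = 40.8%; 0.40/0.80 = 50.0% | 0 → −9.2 | 5.0% → 38.7% |
| F | 15%, unrelated to response | 55%; 35% | 20.0 → 20.0 | 36.7% → 31.5% |

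In E, the group with more early failures looks like the better responder. The rejection rates are approximate, since few complete responses are expected: 84 × (0.25 × 0.05 + 0.75 × 0.03) = 2.9 in A.

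**5. Scale matters.** Take progression of 40% against 20%, with half of all progressors lost in each subtype. Observed: 0.20/0.80 = 25% and 0.10/0.90 = 11.1%. The difference falls from 20 to 13.9 points. The odds ratio is (0.40/0.60)/(0.20/0.80) = 2.67 before and (0.25/0.75)/(0.111/0.889) = 2.67 after. The risk ratio rises from 2.0 to 25/11.1 = 2.25.

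**The case against.** **Exclusion is not stated.** The article nowhere says that a patient without a T5 scan is dropped. Such patients could be coded as progressive disease under a rule in the full protocol or analysis plan, which commonly hold rules for non-evaluable patients. This stands as a limit on the wording: the loss follows from the definition as written and is not a declared intention. It does not remove the point, because the article itself fixes the response variable (two scans, lesion change, four closed categories), and that definition leaves these patients without a value.

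**Bias towards no difference.** A reader might infer that losing early failures must shrink the contrast between subtypes. The documents do not support this, because they do not say how early failure is spread over the subtypes. Scenarios A and C narrow the difference, B and D widen it, E creates one and F leaves it unchanged. Even where half of all progressors are lost in each subtype, the odds ratio is intact.

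**About 21 of 104 lost.** A reader might take 20% of 104 = 20.8 as the number without a T5 scan. The allowance was made for the GUS sample size. Table 2 lists scans under regular treatment, so a patient who stops study sampling may still be scanned. The CMS test also needs archived tissue, so its denominator may be smaller. The attribution to the advanced setting makes disease-related loss plausible but does not measure it.

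**Early deaths count in overall survival.** True, and the Kaplan-Meier curves by subtype will show them. That does not repair the response test, which is a separate analysis under the same objective, and it does not record early progression in patients who remain alive.

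**Conclusion.** The point holds in conditional form. The article defines response only by target-lesion change between T1 and T5, with no place for patients who die or stop for progression before T5. Applied as written, these early failures have no response value and are lost to a test that serves a primary objective. Because the loss is related to outcome, the test can be biased towards the null or away from it, and it can show a spurious difference if early failure differs by subtype.

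The size cannot be derived from the documents. The range of 14.9 to 27.9 points for a true 20-point difference, and the rise in false rejection from 5% to about 39%, rest on assumed response rates, an assumed CMS4 share, an assumed N of 84 and early losses of 2–20% per group. They show the possible directions and do not forecast the result. Since the direction cannot be known in advance, the rule should be settled before response by subtype is examined.

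**What to change.** Add a short rule to the analysis section:

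- The CMS–response analysis includes all treated patients with a CMS result.
- For this analysis, death from disease or documented clinical or radiological progression before T5, including stopping for progression, counts as progressive disease.
- Patients without a T5 scan for any other reason are reported as not evaluable, with numbers and reasons by CMS subtype.
- A sensitivity analysis repeats the comparison as responder (complete or partial response) against non-responder, counting the not-evaluable patients as non-responders.

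The cost is small. Dates of death are already needed for overall survival, and clinical information is already to be completed from medical records, so no extra visit, scan or sample is required. The downside is that clinical progression is less objective than a measured scan. The date and the basis of each such classification should therefore be recorded.

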#### Questionnaires

During the study period, patients are asked to fill out questionnaires at T1, T5, and T6 (Table 1). Amongst others, the questionnaires encompass questions concerning medical history, comorbidities, dietary patterns, the use of pre-/probiotics, the use of antibiotics and other co-medication, smoking, and alcohol use. Furthermore, patients are asked to score their physical functioning (based on the Karnofsky Performance Score, KPS), the risk of malnutrition (based on the MUST), as well as the occurrence of systemic and gastrointestinal toxicity (based on the CTCAE criteria, version 5.0 [24]). Furthermore, the European Organization for Research and Treatment of Cancer (EORTC) QLQ-C30 and the EQ-5D-5L questionnaires are used to quantify QoL.

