**Methods:**

This prospective, observational, multi-center cohort study will include patients with advanced CRC scheduled for irinotecan-based systemic treatment. Archived tumor tissue and routine CT/MRI scans at baseline and after four cycles will be used to investigate the association of tumor molecular profile and treatment response according to RECIST. Before treatment initiation, germline DNA obtained from whole blood will be genotyped using PCR to determine the *UGT1A1*28* genotype, followed by 30% irinotecan dose reduction in UGT1A1 PMs. Bacterial GUS activity will be quantified in fecal samples collected before and during treatment by means of an enzyme activity assay and will be related to patient-reported gastrointestinal toxicity (mainly diarrhea). Additionally, patients will fill in questionnaires concerning QoL, medication use, medical history and comorbidities, dietary habits, as well as physical performance. OS will be documented, capturing the duration from the start of treatment until death from any cause.

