## Background

Colorectal cancer (CRC) represents a major public health concern as it is the third most frequently diagnosed cancer and the second cause of cancer-related mortality worldwide [1]. In 2022, 21% of patients with newly diagnosed CRC in the Netherlands suffered from metastatic disease [2]. In this group of patients, irinotecan-based systemic treatments are commonly applied to relieve symptoms, improve quality of life (QoL) and extend overall survival (OS).

However, the individual response to irinotecan-based treatment differs consistently between patients, and is currently largely unpredictable. Previous research indicated that molecular tumor characteristics might be associated with response to irinotecan-based systemic treatment. CRC can be subdivided into four consensus molecular subtypes (CMS1-4), based on different gene expression profiles [3]. Ten Hoorn et al. concluded based on a meta-analysis that specifically in CMS4 metastatic disease, patients benefit more from irinotecan-based regimens compared with oxaliplatin-containing regimens [4].

An additional disadvantage of irinotecan-based systemic treatment is the occurrence of systemic (primarily neutropenia) and late-onset gastrointestinal (GI) toxicity, (primarily diarrhea). For instance, grade 3–4 neutropenia has been previously identified in 46% and grade 3–4 diarrhea in approximately 18% of patients [5, 6]. The occurrence of severe toxicity often leads to irinotecan dose reduction, or premature discontinuation of the treatment. This negatively affects not only the patient’s QoL and OS, but also puts significant pressure on family and caregivers, as well as on hospitalization-related healthcare costs [7]. Consequently, there is an urgent need for biomarkers to identify patients at risk for developing irinotecan-induced toxicity. In this context, two promising candidate biomarkers are 1) the UDP Glucuronosyltransferase Family 1 Member A1 (*UGT1A1*) genotype of the patient and 2) the microbial enzyme β-glucuronidase (GUS).

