#### Additional information

If available, blood inflammatory markers (e.g. leukocyte counts) will be retrieved from the medical records of participating patients. Furthermore, clinical information derived from the questionnaire will be completed with relevant data from the medical records.

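### Toxicity, the outcome of two primary objectives, is scheduled for scoring only by patient questionnaire at baseline, cycle 4 and cycle 6, so severe diarrhea in cycles 1–3 and neutropenia are at risk of incomplete, outcome-dependent capture

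*Protocol article*

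**What the plan says.** All references are to the protocol article.

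- **Schedule.** The Questionnaires section states: "During the study period, patients are asked to fill out questionnaires at T1, T5, and T6 (Table 1"). The time points are in fact in Table 2, which places T1 at baseline, T5 in cycle 4 and T6 in cycle 6. Table 2 schedules stool at T1 to T6, which adds cycles 1, 2 and 3, and a hospital visit in every cycle.
- **Instrument.** Among the items patients score in these questionnaires is "the occurrence of systemic and gastrointestinal toxicity (based on the CTCAE criteria, version 5.0 [24"]). The abstract says that GUS activity "will be related to patient-reported gastrointestinal toxicity (mainly diarrhea").
- **Second source.** Under Additional information, "clinical information derived from the questionnaire will be completed with relevant data from the medical records". The same section says: "If available, blood inflammatory markers (e.g. leukocyte counts) will be retrieved from the medical records of participating patients".
- **ANC in care.** The UGT1A1 genotyping section says that the dose in poor metabolizers (PMs) is "further individualized in subsequent cycles of treatment based on ANC and clinical tolerance".
- **Consequence of severe toxicity.** The Background says: "The occurrence of severe toxicity often leads to irinotecan dose reduction, or premature discontinuation of the treatment".
- **Use of the outcome.** Under Aims of the study, toxicity is an outcome of the UGT1A1 safety objective and of the GUS objective. The sample size calculation rests on the number of patients with grade 3–4 diarrhea.

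**The concern.** The exposure and the outcome are on different schedules. GUS activity is measured in cycles 1, 2, 3, 4 and 6, but toxicity is scheduled for scoring after baseline only in cycles 4 and 6. The GUS values from cycles 1–3 therefore have no concurrent outcome score.

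Patients who stop before cycle 4 have no scheduled score after baseline at all. Because the article itself ties stopping to severe toxicity, these patients are plausibly enriched for the events that the GUS analysis needs. Loss of that kind depends on the outcome. It can distort the estimated sensitivity and specificity and the GUS–toxicity association, and it also reduces precision.

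The UGT1A1 objective has a further difficulty. The Background names neutropenia as the main systemic toxicity and the one associated with the genotype, but neutropenia is a laboratory finding that a patient cannot grade on a form. The Discussion treats similar rates of severe toxicity in PMs and in full-dose patients as support for the strategy, so incomplete recording bears directly on that conclusion.

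**Working it through.** **1. Schedule side by side (Table 2 and the Questionnaires section)**

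| | Baseline | C1 | C2 | C3 | C4 | C5 | C6 |
|---|---|---|---|---|---|---|---|
| Stool (GUS) | T1 | T2 | T3 | T4 | T5 | – | T6 |
| Questionnaire (toxicity) | T1 | – | – | – | T5 | – | T6 |

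There are two toxicity scores after baseline in six cycles. Three cycles precede the first of them. With the cycle lengths in Table 1 and no delays, cycle 4 runs from 3 × 2 = 6 to 4 × 2 = 8 weeks after the start on two-week regimens, and from 3 × 3 = 9 to 4 × 3 = 12 weeks on irinotecan monotherapy.

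**2. What the records provision fixes**

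The article says that questionnaire information is supplemented from medical records. It names no toxicity item, grade or cycle. Leukocyte counts are to be retrieved where available, as inflammatory markers. ANC and neutropenia grade are not named as collected data, although ANC is used in care. The recall period of the questionnaire is not stated.

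**3. The article's own precision figures**

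The Wald half-width is 1.96 × √(p(1 − p)/n). The article does not state the sensitivity or specificity it assumed; a value of 0.80 reproduces its figures.

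- Sensitivity, 22 cases: 1.96 × √(0.16/22) = 0.167 (stated: 17%).
- Specificity, 62 non-cases: 1.96 × √(0.16/62) = 0.100 (stated: about 10%).

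At a rate of 18%, 84 patients yield 84 × 0.18 = 15.1 severe cases, not 22. That mismatch is a separate matter. It is why the illustration below starts at about 20 points and not at 17.

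**4. Illustration of incomplete capture**

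Let f be the share of severe cases that are captured. The documents give no value for f and no timing of severe diarrhea by cycle, so every f below 1 is an assumption. Recorded cases = 84 × rate × f, with sensitivity taken as 0.80.

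| f | Recorded cases at 18% | Half-width at 18% | Recorded cases, rates 16–22% | Half-width, rates 16–22% |
|---|---|---|---|---|
| 1.00 | 15.1 | 0.202 | 13.4–18.5 | 0.21–0.18 |
| 0.75 | 11.3 | 0.233 | 10.1–13.9 | 0.25–0.21 |
| 0.50 | 7.6 | 0.285 | 6.7–9.2 | 0.30–0.26 |

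For f = 0.50 at 18%: 1.96 × √(0.16/7.56) = 0.285.

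**5. If uncaptured cases were analysed as non-cases**

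The article does not say that they would be. If they were, with true sensitivity and specificity both 0.80 and f = 0.50, the 68.9 true non-cases (84 − 15.1) would be joined by 7.6 missed cases. Apparent specificity would be (0.80 × 68.9 + 0.20 × 7.6)/76.4 = 0.74 instead of 0.80.

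**The case against.** The strongest reply is that there is a second source. Toxicity is a questionnaire item, so the sentence on completion from medical records covers it on a plain reading. Visits take place in every cycle and ANC is in routine use, so the records can contain early severe diarrhea and neutropenia. The article is also a condensed account, and the abstraction fields may well be set out in the full protocol or the case report form. Further, the recall period is unknown: if the cycle 4 form asks about everything since the start, cycles 1–3 are covered for patients who reach it. The planned analysis of toxicity experienced during treatment fits that reading.

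Much of this stands, and it rules out three stronger conclusions that a reader might draw.

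- **That early severe events and neutropenia are missed.** The records and the recall period may recover some or all of them.
- **That patients who stop early are counted as drop-outs or non-cases.** No section says how they are classified, and the sample size section attributes its 20% drop-out to the advanced setting.
- **That the comparison with literature controls falsely favours the reduced starting dose.** That would require those controls to have been graded more completely, for example as worst-ever toxicity, and the article does not say how they were graded. In the second planned comparison, PMs against non-PMs in this study, both groups follow the same schedule, so no asymmetry is built in.

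The reply does not remove the stated schedule. A patient who stops before cycle 4 has no scheduled post-baseline questionnaire whatever recall period the form uses. A retrospective item in cycle 4 would still leave recall error over three cycles. The point therefore rests on what the article fixes, not only on what it leaves unsaid.

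**Conclusion.** The point holds as a risk of incomplete, outcome-dependent capture. Toxicity is the outcome of two primary objectives, its only scheduled scoring is by patients at baseline, cycle 4 and cycle 6, and the article links severe toxicity to stopping. The provision for records may recover some events, but as written it does not fix toxicity grades or ANC as collected items.

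The size of the loss is unknown. If half of about 15 expected severe cases were not captured, the half-width for sensitivity would grow from about 20 to about 29 points (26 to 30 across rates of 16–22%). This assumes 84 evaluable patients, a sensitivity of 0.80 and an arbitrary capture share. If all events were recovered from records, the loss would be nil.

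For the comparison within the study, equal under-recording in PMs and non-PMs multiplies the difference in rates by f and so shrinks it towards zero. That makes the groups look more alike but does not by itself favour one of them.

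The matter should be settled while data are being collected, because concurrent patient reports from cycles 1–3 cannot be recreated afterwards.

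**What to change.** 1. Add a short CTCAE-based diarrhea item, worst grade since the last sample, to the existing stool collections at T2, T3 and T4. State the recall period of the T5 and T6 questionnaires.
2. Define the GI outcome as the worst grade from cycle 1 to cycle 6 or discontinuation, taken from the questionnaires and the medical records together.
3. Keep patients who stop early in the analysis with their worst recorded grade. Count them as cases only if they meet the grade 3–4 diarrhea definition. Counting every stop for toxicity as a case would be wrong, because a patient who stops for neutropenia would then enter the GUS analysis as a diarrhea case.
4. Grade neutropenia from routinely recorded ANC, in the same way for PMs and non-PMs.
5. Correct the cross-reference in the Questionnaires section from Table 1 to Table 2.

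The cost is one brief item at three existing stool collections, some record abstraction and a minor amendment. The added burden on patients is small. Where the full protocol or case report form already specifies items 2 to 4, a statement to that effect is enough for those items.
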